### Sample size

The study is designed to detect a clinically meaningful difference between standard and imaging guided LV lead positioning in CRT as measured by applying a clinical composite endpoint. The underlying assumptions for the primary endpoint are based on data from previous trials in comparable patient cohorts demonstrating a 50 to 70% response rate to CRT [1,2,4,30]. Accordingly, we expect a 60% response rate in the group with empiric LV lead placement and hypothesize an 80% response rate in the group with imaging guided LV lead positioning. Thus, we estimate a 20% difference in the percentage of patients reaching the primary endpoint. To identify this increase in response rate and to achieve a statistical power of 80% a sample size of 182 patients is needed (given a two-sided alpha value of 0.05). The sample size calculation does not account for the stratified randomization [31]. To compensate for an expected loss of follow-up in approximately 5% of the patients, a total of 192 patients are included. Sample size calculation was performed using commercially available statistical software (Stata version 12, StataCorp, College Station, TX, USA) to estimate the sample size for a two-sample comparison of proportions.

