### Randomization and blinding procedure

Patients are randomized using a randomization module in the eCRF. An external data manager is responsible for the eCRF, including the randomization module. A random allocation sequence is created using a standard computerized random-number generator. Patients are randomized in a permuted-block design employing different sized blocks. The randomization is stratified according to presence or absence of coronary artery disease (≥50% stenosis of one or more major epicardial arteries as revealed by a recent invasive coronary angiography or medical records documenting a previous myocardial infarction. Invasive coronary angiography is performed before CRT implantation if no recent examination (within two years) is available). The stratified randomization ensures a balance between treatment groups with 50% of patients with coronary artery disease in each group. Study subjects are allocated 1:1 to each intervention arm. Physicians responsible for enrollment of patients have no knowledge of block size or allocation sequence. Information on randomization is available in the implant window of the eCRF. Only the implanting physician has access to this window. When the patient is randomized to imaging guided LV lead placement the implant window contains uploaded images illustrating the LV region with the latest mechanical activation, distribution of scar tissue, and cardiac venous anatomy, respectively. When randomized to empiric LV lead placement the implant window will not show these images; thus, the implanting physician does not have access to information on LV mechanical activation pattern, distribution of scarred myocardium, and coronary venous anatomy prior to CRT implantation.

All baseline and follow-up evaluations, including clinical assessment, image acquisitions and analyses, are blinded with respect to randomization. Patients are blinded to the intervention arm. Randomization data will be available when all patients have completed follow-up.

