### Statistical analysis

Demographic and baseline characteristics of both intervention groups are presented and compared clinically. At follow-up, a Pearson’s *χ*^2^ or Fisher’s exact test when appropriate is used to compare categorical variables. Normally distributed continuous variables are compared using Student’s *t*-test. Continuous variables not normally distributed are compared using a Wilcoxon’s rank-sum test. Forty patients will be randomly selected for assessing intra- and interobserver variability for the dyssynchrony measurements using linear regression and Bland-Altman analysis. In the same 40 patients, kappa statistics are computed to assess intra- and interobserver agreement of site with latest mechanical activation and final LV lead position. All analyses will be conducted according to the intention-to-treat principle. Multiple imputation will be applied in case of missing data [32]. A two-sided *P-*value of <0.05 is considered to be statistically significant. Statistical software (Stata version 12, StataCorp, College Station, TX, USA) is used for statistical analysis.

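### The only test named for the primary endpoint ignores the coronary artery disease stratum; if that stratum predicts response, the test is mildly conservative and gives up a little power

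*Protocol article*

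**What the plan says.** Protocol article, Randomization and blinding procedure: "The randomization is stratified according to presence or absence of coronary artery disease". Allocation is 1:1, in permuted blocks of varying size.

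Protocol article, Endpoints: the primary endpoint is binary. A patient counts as a non-responder after death, heart failure hospitalization, or failure to improve on both functional measures.

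Protocol article, Statistical analysis: Pearson's chi-square or Fisher's "exact test when appropriate is used to compare categorical variables". This general sentence is the only one that covers a binary outcome. The section names no stratified or CAD-adjusted analysis. It also plans intention-to-treat analysis and multiple imputation of missing data.

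Protocol article, Sample size: "The sample size calculation does not account for the stratified randomization". This remark concerns planning only and says nothing about the test to be used.

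**The concern.** Balancing CAD between the arms removes differences in CAD mix from the treatment contrast. An unstratified test still counts the CAD-related variation in its standard error. If CAD predicts response, the standard error is too large, the actual type I error falls below 5%, confidence limits are too wide, and some of the precision bought by stratifying is not used.

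At stake is a modest amount of efficiency in the primary comparison. There is also a procedural benefit in naming the stratified analysis before allocation is revealed, because it removes any later choice between a crude and an adjusted result.

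**Working it through.** **Inputs from the article (Sample size).** Two-sided alpha of 0.05 ("given a two-sided alpha value of 0.05"); 60% response with empiric placement ("we expect a 60% response rate in the group with empiric LV lead placement"); 80% with imaging guidance ("hypothesize an 80% response rate in the group with imaging guided LV lead positioning"); 182 evaluable patients for 80% power ("achieve a statistical power of 80% a sample size of 182 patients is needed"), that is 91 per arm; 192 after allowing for 5% loss.

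**Assumptions.** The article gives no response rates by CAD, so the gap d between non-CAD and CAD patients is varied from 0 to 40 points and taken as equal in both arms. CAD prevalence is set at 50%, with 30%, 40% and 60% as checks.

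**Step 1: the plan's own figure.** Without continuity correction:

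n = [1.96·√(2·0.7·0.3) + 0.8416·√(0.6·0.4 + 0.8·0.2)]² / 0.2² = (1.2702 + 0.5323)² / 0.04 ≈ 81.2, so 82 per arm and 164 in total.

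With continuity correction:

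n' = (81.2/4)·[1 + √(1 + 4/(81.2·0.2))]² ≈ 90.95, so 91 per arm and 182 in total.

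182/0.95 = 191.6, so 192. Both stated figures reproduce with the continuity-corrected formula.

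**Step 2: expected size of the unstratified test.** With overall response p and 50% CAD, the unstratified test uses variance V_total = p(1 − p). Under balanced strata the contrast actually has V_within = p(1 − p) − d²/4. The actual size is 2·[1 − Φ(1.96·√(V_total/V_within))].

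For p = 0.60 and d = 0.20: V_total = 0.24 and V_within = 0.24 − 0.01 = 0.23. √(0.24/0.23) = 1.0215, so the effective critical value is 2.002 and the size is 0.0453. The standard error is about 2% too large. For d = 0.30: V_within = 0.2175, the root is 1.0505, and the size is 0.0395. The standard error is about 5% too large.

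**Step 3: simulation.** 400,000 replicates per scenario, 91 per arm, 1:1 balance within strata, no missing data, Pearson without continuity correction.

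| Gap d (points) | V_within/V_total at 60% | Type I error at 60%: Pearson | Type I error at 60%: CMH | Power at 60% vs 80%: Pearson | Power at 60% vs 80%: CMH |
|---|---|---|---|---|---|
| 0 | 1.000 | 0.0512 | 0.0501 | 84.7% | 84.5% |
| 10 | 0.990 | 0.0492 | 0.0505 | 84.7% | 84.8% |
| 20 | 0.958 | 0.0458 | 0.0515 | 85.2% | 86.4% |
| 30 | 0.906 | 0.0400 | 0.0494 | 86.0% | 88.6% |
| 40 | 0.833 | 0.0321 | 0.0499 | 87.2% | 91.9% |

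The simulated sizes agree with the formula in Step 2. A second simulation of the 0 to 30 point scenarios gave power within 0.3 points of these values.

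**Step 4: sensitivity.**
- Overall response 70%: Pearson size 0.0449 at 20 points and 0.0381 at 30.
- CAD prevalence 30%, 40% or 60%, 20-point gap, 60% response: Pearson size 0.046 to 0.048.
- All 192 patients evaluable, 20-point gap: power 87.2% for Pearson against 88.1% for CMH.

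**Step 5: which gaps are feasible.** At 30 points and 50% CAD, the imaging-guided arm would need 95% response without CAD and 65% with it. At 40 points it would need 100% and 60%. The last rows of the table are therefore edge cases.

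**The case against.** Four counter-arguments deserve weight.

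**The effect is conditional.** It vanishes if CAD does not predict this composite endpoint, and the article gives no CAD-specific rates. Its stated reason for stratifying is balance between arms. The Discussion links lead placement in transmural scar to poor outcome, and the CAD stratum includes patients with previous infarction. That makes a gap plausible but does not quantify it. This argument stands, and the point has to be stated conditionally.

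**The error is on the safe side.** A reader might infer from a size that differs from 5% that the primary test is invalid or inflates false positives. The calculations do not support this: the size is nominal with no gap and falls as the gap grows. A significant unstratified result would remain credible.

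**The design is not threatened.** A reader might also infer that the trial is underpowered. Uncorrected Pearson power is at least 84% at 182 patients in every scenario, because 182 already includes a continuity-correction margin over 164. The admission that the sample size ignores stratification is not a contradiction either, since planning and named test are both unstratified two-sample comparisons.

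**The article is condensed.** The test sentence is generic, and a fuller protocol or analysis plan could specify a stratified primary analysis. The article does not rule one out. This weakens the point without removing it: the published text does name a test for binary outcomes, and that test does not follow the randomization.

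**Conclusion.** The point holds as a low-cost improvement and not as a flaw in validity. Allocation is stratified by CAD, and the only test named for the primary endpoint is not.

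If CAD predicts response, that test is conservative: type I error about 4.6% for a 20-point gap and 4.0% for 30 points, against about 5% for CMH. The power cost is about 0 to 1 point for gaps up to 20 points and about 2.5 points at 30. If CAD does not predict response, nothing is lost.

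These sizes rest on an assumed gap, equal in both arms, and on an assumed 50% CAD prevalence. The article's sentence about 50% of patients with CAD in each group is ambiguous, because stratification balances CAD between arms without fixing its prevalence. The 20-point result hardly changes between 30% and 60% CAD. The figures apply to the uncorrected Pearson test; Fisher's test was not simulated.

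**What to change.** In Statistical analysis, name the primary test separately from the generic sentence on categorical variables:

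- Primary: a Cochran-Mantel-Haenszel test of non-response stratified by CAD as recorded at randomization, reported with the stratum-weighted risk difference and its 95% confidence interval.
- Where multiple imputation is used, state how the test and the risk difference are pooled across imputations.
- Sensitivity: the crude Pearson test.

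A regression with treatment and CAD is an acceptable alternative but not an equivalent one. Logistic regression estimates an odds ratio conditional on CAD, which is a different quantity from a risk difference, so the plan should say which is the primary effect measure.

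The cost is a few sentences. The stratifier is already recorded, and no data or patients are added. If CAD turns out not to matter, the price is negligible (84.5% against 84.7% power in simulation). The change should be fixed before the randomization data are released, which the article places after all patients complete follow-up.

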### Echocardiography

Baseline and follow-up echocardiographic images are obtained at rest with a 3.5-MHz transducer using a commercially available system (Vivid E9, GE Medical Systems, Horten, Norway). Two-dimensional (2D), color Doppler and tissue Doppler imaging (TDI) data triggered to the ECG are stored in cine-loop format and transferred to a workstation for offline analysis using dedicated software (EchoPac BT11, GE Medical Systems, Horten, Norway). At least three consecutive beats are recorded during breath hold in all views. All measurements are averaged over three cycles.

LV end-diastolic volume (EDV) and end-systolic volume (ESV) are assessed from standard apical four- and two-chamber views. LV EF is estimated using Simpson’s biplane method [24]. Severity of mitral regurgitation is graded semi-quantitatively [25].

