### Follow-up

The device is tested at day one, one month and six months after implantation to ensure sufficient biventricular pacing (>95% of the time). Atrioventricular (AV) and interventricular (VV) optimization is performed at day one and repeated after one month. Optimal AV delay is obtained by the iterative method using transmitral pulsed wave Doppler to achieve the longest LV filling time with adequate E- and A-wave separation and termination of the A-wave. Optimal VV delay is programmed by changing the V-V sequence measuring the highest LV outflow tract time-velocity integral [28].

At six months follow-up, clinical, functional and echocardiographic variables are assessed as performed at baseline. LV lead position is assessed by cardiac CT as described and categorized as concordant (located at the optimal LV pacing site), as adjacent (one segment away) and remote (≥2 segments away from the optimal LV pacing site).

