### Endpoints

The primary endpoint is non-response to CRT defined as the combination of all-cause mortality, hospitalization for heart failure, and unchanged or worsened functional status. The primary endpoint is attained if the patient is registered for one of the following three events during follow-up: (1) death from any cause, (2) hospitalization for heart failure, or (3) no improvement in NYHA class *and* <10% improvement in 6MWT.

Hospitalization for heart failure is defined as admission to the hospital lasting more than 24 hours with symptoms of congestive heart failure and subsequent intravenous treatment for heart failure.

Secondary endpoints include all-cause mortality, hospitalization for heart failure and changes of the following variables during follow-up: NYHA class, 6MWT, quality of life, Nt-ProBNP, LV EF, LV EDV and ESV, LV dyssynchrony and mitral regurgitation grade. Also, procedure time for CRT implantation, ability to place the LV lead in the first or second prioritized CS branch, complications and final lead positions are recorded.

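### The test rules make no provision for ordered scales, so read literally NYHA class and mitral regurgitation grade get a test that ignores order (minor)

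*Protocol article*

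**What the plan says.** The Statistical analysis section of the protocol article chooses the follow-up test by type of variable:

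- Categorical: Pearson's chi-square, or Fisher's "exact test when appropriate is used to compare categorical variables".
- Continuous and normally distributed: Student's t-test.
- Otherwise: "Continuous variables not normally distributed are compared using a" Wilcoxon rank-sum test.

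There is no rule for ordered categories, and no individual endpoint is assigned to a rule.

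The Endpoints section reads: "Secondary endpoints include all-cause mortality, hospitalization for heart failure and changes of the following variables during follow-up: NYHA class, 6MWT, quality of life". The same list ends with "LV dyssynchrony and mitral regurgitation grade". NYHA class and regurgitation grade are therefore secondary endpoints, expressed as changes. The Echocardiography section adds: "Severity of mitral regurgitation is graded semi-quantitatively". It does not give the number of levels.

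**The concern.** NYHA class and a semi-quantitative regurgitation grade are short ordered scales. They are not continuous, so the rank-sum rule as worded does not reach them, and the rule that remains is chi-square or Fisher. On a two-by-K table the general Pearson test uses K − 1 degrees of freedom and gives the same P-value however the columns are arranged. If guided placement moves patients steadily towards better classes or less regurgitation, that test spreads its sensitivity over patterns nobody expects. It also yields no single effect estimate with a direction.

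At stake is power, and a readable effect measure, for two named secondary endpoints. The trial was sized for a binary primary endpoint, so these endpoints have no power reserve planned for them.

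**Working it through.** **1. The plan's own figure.** The Sample size section gives 60% against 80% response, 80% power, two-sided alpha 0.05, 182 patients, and 192 after about 5% loss.

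- Uncorrected, per arm: [1.96·√(2·0.7·0.3) + 0.8416·√(0.6·0.4 + 0.8·0.2)]² / 0.2² = (1.270 + 0.532)² / 0.04 ≈ 81.2, so 82 per arm (164 in total). This does not match.
- With continuity correction: (81.2/4)·[1 + √(1 + 4/(81.2·0.2))]² ≈ 90.95, so 91 per arm and 182 in total. This matches.
- 182/0.95 = 191.6, so 192. This matches.

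The sample size rests on the binary endpoint, for which chi-square is suitable. The figure of 91 per arm is used below.

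**2. Assumptions.** The article gives no distribution for either scale, so these are illustrative. Each has a common odds ratio (OR) of 2 applied to every cumulative split.

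- Four levels (NYHA-like): control 15/50/30/5%. Cumulative 0.15, 0.65, 0.95 become 0.261, 0.788, 0.974, giving 26.1/52.7/18.6/2.6%.
- Five levels (regurgitation-like): control 25/35/20/15/5%, giving 40.0/35.0/13.9/8.5/2.6%.

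**3. Simulated power.** 91 per arm, 20,000 runs, two-sided 0.05, Pearson chi-square on the full table against the tie-corrected, unadjusted rank-sum test:

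| Scale | OR | Chi-square | Rank-sum | Difference (points) |
|---|---|---|---|---|
| Four levels | 1.5 | 19% | 30% | 11 |
| Four levels | 2.0 | 52% | 69% | 17 |
| Four levels | 2.5 | 78% | 90% | 12 |
| Five levels | 1.5 | 18% | 32% | 14 |
| Five levels | 2.0 | 50% | 73% | 23 |
| Five levels | 2.5 | 77% | 92% | 15 |

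With no effect, both tests reject in about 5% of runs.

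**4. Check by formula.** The noncentrality of the Pearson statistic is n·Σ(p − q)²/(p + q), where p and q are the control and guided proportions.

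- Four levels, OR 2: 91·(0.0299 + 0.0007 + 0.0265 + 0.0079) ≈ 5.9. On 3 degrees of freedom (critical value 7.81) this gives 51% power. If nearly all of it is captured on 1 degree of freedom (3.84), power is 68%.
- Five levels, OR 2: 91·(0.0346 + 0 + 0.0110 + 0.0177 + 0.0079) ≈ 6.5. On 4 degrees of freedom (9.49) this gives 50%, against 72% on 1 degree of freedom.

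Both agree with the simulation. The loss comes from the extra degrees of freedom.

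**5. Does analysing change remove the problem?** No. Change in class is itself a short ordered scale. A simulation on a four-level change scale with OR 2 gave 52% against 69%.

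**The case against.** **The assignment is an inference.** The Statistical analysis section never names NYHA class or regurgitation grade. A change in grade could be scored and ranked, and a condensed article often leaves such allocation to the analysis plan. This stands in part. One cannot say that the sponsor will use chi-square here, only that the rule as worded leads there. But the article is not silent: it sets rules by variable type and confines the rank test to continuous variables, so the wording needs amending even if ranks were intended.

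**The power loss is not general.** This stands. It assumes a shift in one direction and depends on the number of levels. If each endpoint were reduced to improved or not improved, no order would be left to lose.

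A reader might infer three stronger points that the document does not support:

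- *That lead position is affected in the same way.* The Follow-up section has it "categorized as concordant (located at the optimal LV pacing site), as adjacent (one segment away) and remote", which is ordered. But the Endpoints section says only that "complications and final lead positions are recorded", and a rank test is not reliably better for it. If adjacent leads become concordant and remote ones stay fixed (45/35/20% to 65/15/20%), chi-square has about 85% power and rank-sum about 54%.
- *That the plan ignores baseline grade.* The endpoints are defined as changes, so baseline is already used in part.
- *That the test is invalid or the main result is at risk.* Type I error is nominal for both tests, and the primary endpoint is binary.

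That chi-square gives no direction is a small matter, since the table printed beside it would show one.

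**Conclusion.** The point holds as a minor one. The stated rules have no place for ordered outcomes and, taken literally, send NYHA class and mitral regurgitation grade to a valid test that is blind to order. Under an assumed one-directional shift with an odds ratio near 2 and 91 per arm, the cost is roughly 17 points of power with four levels and 23 with five. Across odds ratios from 1.5 to 2.5 it is about 11 to 23 points.

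These figures rest on assumed category distributions, a uniform shift and an unadjusted rank-sum comparator. The gain from a covariate-adjusted model was not calculated. The primary analysis, the 182/192 sample size and type I error do not change.

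**What to change.** Add one sentence to the Statistical analysis section, settled before the randomization data are released, saying that NYHA class and mitral regurgitation grade are compared by a method that respects order. Either of these would do:

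- proportional-odds regression of the six-month grade on treatment, baseline grade and the coronary artery disease stratum, reporting the common odds ratio with its 95% confidence interval; or
- a rank-sum test stratified by coronary artery disease, on the six-month grade or on change in grade, if proportional odds is doubtful.

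Keep chi-square or Fisher for binary and nominal variables.

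The cost is small: no new data, visits or patients. The regression brings the proportional-odds assumption and models the six-month grade given baseline, where the Endpoints section speaks of change, so that description should be aligned. The stratified rank test on change needs no such alignment.

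### Continuous secondary endpoints are compared by unadjusted tests that use neither the baseline value nor the randomization stratum as a covariate, which is valid but gives up precision

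*Protocol article*

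**What the plan says.** The Endpoints section of the protocol article lists as secondary endpoints all-cause mortality, "hospitalization for heart failure and changes of the following variables during follow-up". The continuous ones are the six-minute walk, quality of life, NT-proBNP, ejection fraction, end-diastolic and end-systolic volumes, and dyssynchrony. Under Follow-up, at six months, "clinical, functional and echocardiographic variables are assessed as performed at baseline", so each variable has one baseline and one six-month value obtained in the same way.

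The Statistical analysis section names Student's t-test for normally distributed variables. For the rest, "Continuous variables not normally distributed are compared using a Wilcoxon" rank-sum test. It does not say whether these tests are applied to the change or to the six-month value, and it gives no criterion for judging normality. Regression appears in that section only for observer variability. Randomization is stratified by coronary artery disease (Randomization and blinding procedure), but the named tests do not use the stratum.

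**The concern.** A two-sample test of change uses the baseline only by subtraction, which amounts to fixing the regression slope on baseline at 1. When the true slope differs from 1, the test leaves variance in the comparison that a baseline covariate would remove. It also leaves part of any chance baseline imbalance in the estimate from the one trial that is run.

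The sample size was set for the binary primary endpoint alone, so the precision of the functional and remodeling results depends on how they are analysed. The Discussion part of the abstract presents the trial as assessing an echocardiographic as well as a clinical effect, and these endpoints supply the echocardiographic part.

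A second, separate matter is that the two named tests answer different questions. The t-test concerns a difference in means. The rank-sum test does not, and it yields no mean difference with a confidence interval. If the observed distribution decides between them, the reported effect measure for each endpoint is settled only after the data are in.

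**Working it through.** **The plan's own figure.** The inputs are in the Sample size section: "we expect a 60% response rate in the group with empiric LV lead placement and hypothesize an 80% response rate" with imaging guidance, "given a two-sided alpha value of 0.05", and 80% power; allocation is 1:1.
- Uncorrected two-proportion formula: [1.96·√(2·0.7·0.3) + 0.8416·√(0.6·0.4 + 0.8·0.2)]² / 0.2² = 81.2, so 82 per arm or 164 in total.
- With continuity correction: (81.2/4)·[1 + √(1 + 4/(81.2·0.2))]² = 90.9, so 91 per arm or 182 in total, as stated.
- Allowance for 5% loss: 182/0.95 = 191.6, so 192, as stated.

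These figures concern the binary primary endpoint. The point made here does not change them.

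**Precision of the continuous comparisons.** The documents give neither an SD nor a correlation. Assume equal SDs at baseline and six months, and a correlation r between them of 0.5 to 0.8. In units of the common variance, and apart from a factor shared by all three methods, the large-sample variance of the treatment contrast is:
- six-month value alone: 1
- change score: 2(1−r)
- analysis of covariance (ANCOVA): 1−r²

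Hence ANCOVA/change = (1−r²)/[2(1−r)] = (1+r)/2, and ANCOVA/six-month value = 1−r².

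| r | Change | ANCOVA | ANCOVA/change | 182 patients are worth |
|---|---|---|---|---|
| 0.5 | 1.00 | 0.75 | 0.75 | 182/0.75 = 243 |
| 0.6 | 0.80 | 0.64 | 0.80 | 182/0.80 = 228 |
| 0.7 | 0.60 | 0.51 | 0.85 | 182/0.85 = 214 |
| 0.8 | 0.40 | 0.36 | 0.90 | 182/0.90 = 202 |

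Outside that range, the ratio to the change score is 0.65 at r = 0.3 and 0.95 at r = 0.9. Confidence intervals scale with the square root of the ratio: √0.75 = 0.87 and √0.90 = 0.95, so they are about 13% to 5% narrower.

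**In terms of power.** For an assumed difference of 0.4 SD with 91 per arm (normal approximation), power at r = 0.5 is 77% for change and 88% for ANCOVA. At r = 0.7 it is 94% and 97%.

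**If six-month values alone were tested.** The ratio is then 1−r²: 0.75, 0.64, 0.51 and 0.36 for r = 0.5, 0.6, 0.7 and 0.8. At r = 0.7, 182 patients would be worth 182/0.51 = 357. This applies only under that reading.

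**Equal-SD assumption.** Let k be the six-month SD divided by the baseline SD. In units of baseline variance, the change score has variance 1 + k² − 2rk and ANCOVA has k²(1−r²). The excess is (1−rk)². It is never negative, but it can vanish: at r = 0.8 and k = 1.25, rk = 1 and the gain is zero.

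**Choosing the test by normality.** A two-stage rule was simulated under no treatment effect: Shapiro-Wilk at 5% in each arm, then a t-test if both arms passed and a rank-sum test otherwise. There were 91 patients per arm and 8,000 runs per distribution. The rejection rate was 4.9% for normal, 4.8% for lognormal and 5.1% for mildly skewed gamma data.

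**The case against.** The strongest defence is that nothing invalid is planned. A two-sample test of change is unbiased under randomization and holds its level, and its standard error already reflects chance baseline imbalance. All the endpoints concerned are secondary, and no power is claimed for them. The article is condensed and a statistical analysis plan may exist. Details such as transformations and sensitivity analyses commonly belong there, so their absence is no fault. All of this stands. It does not remove the point, because the article does name a method for these variables and that method is unadjusted. A plan that followed it would carry the same loss.

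A reader might infer three stronger things, none of which the documents support:
- **That baseline values are ignored.** The Endpoints section defines these endpoints as changes, so the baseline enters by subtraction. The accurate statement is that it is not used as a covariate.
- **That the loss is as large as 1−r² suggests.** This needs the tests to be run on six-month values alone. The Statistical analysis section leaves the tested quantity unsaid, but read with the Endpoints section the change is the natural meaning.
- **That choosing the test by normality inflates the false-positive rate or itself costs precision.** The simulation showed no inflation, and no precision loss from the choice was calculated. For skewed variables a rank test can be the more efficient of the two.

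**Conclusion.** The concern holds as a matter of efficiency, not validity. For the continuous secondary endpoints, leaving out the baseline covariate costs a moderate amount of precision. ANCOVA would have 0.75 to 0.90 of the variance of the change-score t-test, given an assumed r of 0.5 to 0.8 and equal SDs at both visits. The direction is secure, because in large samples adjustment does not do worse. The size is not secure, because the documents supply neither r nor the SDs, and in special cases the gain is nil.

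That the distribution chooses between two tests with different targets stands as a separate and smaller weakness of pre-specification: the effect measure is not fixed in advance. The primary endpoint, the 182 evaluable and 192 total patients, and the randomization are unaffected.

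**What to change.** In the Statistical analysis section, and in the statistical analysis plan if it repeats that text:
- Analyse each continuous secondary endpoint by linear regression of the six-month value on arm, its own baseline value and the coronary artery disease stratum. Regressing the change on the same terms gives the same treatment effect, so this still serves an endpoint defined as change.
- Fix the scale of each variable in advance, for example log NT-proBNP.
- Report the adjusted difference with its 95% CI.
- Replace the rule that picks a test from the observed distribution, and keep the rank-sum test as a sensitivity analysis.

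The cost is a few sentences, settled before the randomization data are released. No new data are needed, since the baseline values and the stratum are already recorded. A regression coefficient and its standard error also combine directly across the multiple imputations that the article already plans.
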